### Interim analyses

Our team will write interim reports at regular six-month intervals throughout the study. These reports will include a summary of project progress, key achievements, preliminary findings, challenges encountered, project timelines, resource utilisation, any necessary methodological adjustments and updates on participant recruitment, retention rates and data quality. The reports will be shared with the key stakeholders.

### Methods for additional analyses (e.g. subgroup analyses)

Not applicable.

### Methods in analysis to handle protocol non-adherence and any statistical methods to handle missing data

All eligible participants with reliable data and complete measures ( < 10% missing) at baseline will be included in the analysis. Participants who move into their long-term accommodation will remain in the study and follow-up will be continued. During the data collection periods we will give special attention to prevent missing data. One of the advantages of GLMMs over ANOVA is that it maximises the number of observations by excluding missing values only, rather than removing complete cases with some or all missing values present. This approach helps to maintain statistical power and reduce bias. In cases where missing data cannot be avoided, we use imputation methods using the mice R package [194] if more than 10% of the values in the entire dataset are missing, but no more than 30% per participant per assessment instrument. This threshold ensures that imputation is used judiciously and only when the amount of missing data is large enough to potentially affect the results, but not so large as to compromise the validity of the imputation process. We will conduct sensitivity analyses to compare results with and without imputation to assess the robustness of our findings. In addition, we will thoroughly document the patterns and reasons for missing data to inform the interpretation of results and discuss any potential biases introduced by missing data.

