**Methods:**

To assess the effect of NAT, we will apply a quasi-experimental parallel group study with a natural waiting list control group (regression discontinuity design). Follow-up assessments will be conducted continuously up to 12 months later, in person and online. The outcomes of the study will include symptoms of depression, anxiety and posttraumatic stress, using the Refugee Health Screener (RHS-15, primary outcome). The study will also assess social and economic integration, and resilience, as well as successful application of the NAT counselling intervention, amongst other measures. Cost-effectiveness and sustainability will be assessed for the overall programme. Sustainability will be measured on the basis of counsellor participation and satisfaction using a mixed methods approach. The study will be conducted at various selected sites in southwest Germany.

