### Implementation

To assign participants according to the RDD principles, we will use the RHS-15 (items 1–13) as eligibility criteria with two critical thresholds at 13 and 36 (see Fig. 4) as foreseen in the stepped-care model of the *NAT counselling intervention*. The RDD then assumes that the allocation to the conditions is nearly random within the determined bandwidth (RHS sum scores just above or below the cutoffs) and potential factors that would manipulate treatment effect vary randomly across participants in both groups. The *fuzzy* versus the *sharp* design version takes into account real-world implementation settings recognizing that participants with RHS scores in the yellow range need to be assigned to the red group, for instance, in cases of suicidal ideation or other negative psychological developments that requires treatment by clinical psychologist.

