#### Assessment (refugees)

Data collection from refugees begins with a face-to-face interview conducted by one of the NAT counsellors (see Sect. Intervention description) and continues with 10-minute monthly online assessments (Well-being Monitor). Approximately 6 to 9 months after the initial screening, refugees will be invited to a face-to-face follow-up interview.

At the start of the face-to-face baseline interview, we will ask for demographic information, screen for trauma related symptoms, and collect information on social and economic integration. The follow-up interview after 6–9 months will re-assess levels of psychological distress and integration.

The 15-item Refugee Health Screener [123] will be used to assess the severity of trauma related reactions. The RHS was adapted from validated instruments for depression, anxiety and PTSD to screen for trauma related reactions in refugee populations. Each item is rated on a scale from 0 (not applicable at all) to 4 (extremely) and a total score of items 1–13 indicates the severity of symptoms (0–52) and the intensity of treatment required. Items ask for instance for nightmares, loss of interest or other trauma related symptoms. Items 14 and 15 are taken into account in a qualitative way. The RHS was recently validated with refugees in the German context [124]. Kaltenbach et al. [124] found high sensitivity and good feasibility, reliability and validity for both the self-rating and interview versions. Strong psychometric properties of the RHS were also found in other studies in Germany [147, 148] and elsewhere [149, 150].

An adapted version of the Appetitive Aggression Scale [139] for refugees will be used to assess aggression. The AAS is a 15 item semi structured interview that measures appetitive aggression according to the extent of agreement to statements, on a scale ranging from 0 (disagree) to 4 (agree) for each item. A total sum score will be used to measure severity of aggression (max 60).

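### The dataset-wide 10% trigger for imputation is the wrong scale for a primary outcome that is a 13-item sum

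*Protocol article*

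**What the plan says.** The missing-data section of the protocol article (the section on protocol non-adherence and missing data) sets three limits.

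- **Baseline inclusion:** participants with "complete measures ( < 10% missing) at baseline will be included in the analysis".
- **Trigger:** multiple imputation with mice is used "if more than 10% of the values in the entire dataset are missing".
- **Cap:** once triggered, values are imputed "but no more than 30% per participant per assessment instrument".

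The section justifies trigger and cap together: imputation is to be used when enough is missing to matter, but not so much that the imputation becomes unreliable. It also promises a comparison of results with and without imputation. It notes that the mixed models drop only the missing values and not whole cases.

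The abstract assesses symptoms "using the Refugee Health Screener (RHS-15, primary outcome". Under Assessment (refugees), items score between 0 and 4, and the severity measure is their sum: "a total score of items 1–13 indicates the severity of symptoms (0–52". Under Implementation, the same total governs allocation: "we will use the RHS-15 (items 1–13) as eligibility criteria with two critical thresholds at 13 and 36".

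**The concern.** This point is about blank items inside a completed follow-up form, not about missed visits. A percentage taken over all values in the file says nothing about whether a given participant's RHS total can be formed. One blank among 13 items is a small share of values, but it makes the whole total incomplete.

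The trigger also moves with content that has nothing to do with the RHS. Table 3 lists eleven instruments, most of them online only, and assessments are monthly. Gaps in a food or literacy scale, or missed online assessments, could switch RHS imputation on or off.

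At stake are the analyses that need one follow-up RHS total per person: the ordinary least squares fits on each side of the cutoff and, where need for treatment is read from the RHS, the chi-squared tests for hypotheses 2a and 2b. The remark that mixed models lose only missing values does not cover these analyses. Even in a mixed model the missing value is the whole total, so 12 answered items can go with the one left blank.

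**Working it through.** **Inputs from the protocol article.** 13 items scored 0–4 (check: 13 × 4 = 52, which agrees with the stated range); trigger 10% of all values; cap 30% per participant per instrument; about 1,500 candidates with 30–50% participating, that is 450 to 750 people. The article gives no item-missing rate and no missing-data pattern, so there is no figure of its own to reproduce. The rate p and the within-form correlation ρ below are assumptions.

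**Step 1: what the limits mean for the RHS.** 1/13 = 7.7%, 2/13 = 15.4%, 3/13 = 23.1%, 4/13 = 30.8%. The 30% cap therefore allows up to 3 blank items. If the baseline rule is read per instrument, it admits one blank item and not two.

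**Step 2: a bound that needs no assumed rate.** Suppose every RHS form lacks exactly one item and all else is complete. If RHS items make up a share w of all values, the dataset-wide missing percentage is w × 7.7%, which is at most 7.7%. That is below 10%, so imputation stays off although no RHS total is complete.

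**Step 3: the reverse case.** If missed assessments count as missing values, they can push the file past 10%. A wholly missed form is 100% missing and lies outside the 30% cap. The trigger could then be set off by gaps that the imputation does not treat.

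**Step 4: how many totals could be affected.** With independent blanks, P(at least one blank) = 1 − (1 − p)^13; at p = 2% this is 1 − 0.98^13 = 23.1%. For clustered blanks, a beta-binomial on 13 items with a = p(1 − ρ)/ρ and b = (1 − p)(1 − ρ)/ρ gives P(any) = 1 − P(0).

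| Item-missing rate p | Any blank: independent | Any blank: ρ = 0.1 | Any blank: ρ = 0.6 | 1–3 blanks (within cap): independent | 1–3 blanks: ρ = 0.6 |
|---|---|---|---|---|---|
| 1% | 12.2% | 8.0% | 2.6% | 12.2% | 1.2% |
| 2% | 23.1% | 15.5% | 5.1% | 23.1% | 2.4% |
| 5% | 48.7% | 34.6% | 12.3% | 48.4% | 5.7% |

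**Step 5: as counts.** At p = 2%, if all 450 to 750 participants completed a follow-up form, 104 to 173 totals would have a blank with independent blanks (23.1%), and 23 to 38 with ρ = 0.6 (5.09% × 450 and × 750). Attrition would lower these counts.

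**The case against.** The strongest reply is that the harm needs a step the article does not contain. It nowhere scores a blank as 0 and nowhere sets such a total to missing. Scoring rules for partly answered scales are commonly left to the analysis plan, and proration could be specified there. This stands, and silence on scoring alone would not be a finding. What remains is a stated rule with a stated reason, and Step 2 shows that the reason fails for this outcome.

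A reader might infer that many totals are lost or scored too low. The documents do not support that. It needs an item-missing rate they do not give, and the shares fall sharply if blanks cluster. A shortfall from scoring a blank as 0 (on average 37/13 = 2.8 points at a true total of 37) would apply only if blanks were scored that way. Bias in the NAT contrast would also need the pattern or handling of blanks to differ between groups, and nothing in the documents shows this.

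Three further objections have weight.

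- The baseline and 6–9 month RHS are taken by counsellors in interviews on tablets, with regular checks for missing values, so item blanks may be rare.
- The trigger may in fact be met once missed assessments are counted. The handling of RHS items would then turn on attrition elsewhere, which supports the point about scale.
- The comparison with and without imputation carries no stated condition and may help, but the article does not say whether it runs below the trigger.

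A reader might also want one scoring rule for baseline and follow-up. That would be unsound. The running variable in a regression discontinuity design must be the score that actually determined allocation, and re-scoring it later could move people across a cutoff by which they were never assigned.

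**Conclusion.** The point holds in a limited form. The trigger is on the wrong scale for a 13-item sum: it can stay off when no RHS total is complete, and it can be switched on by unrelated gaps. Below it, the article leaves partly answered follow-up totals without imputation and without another stated way to form them. Answered items may therefore be lost from the regression discontinuity analysis and the 2a/2b tests.

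The bound of 7.7% against 10% rests only on the article's own numbers. The size of the practical effect is not known: at an assumed 2% item-missing rate, between about 5% (strong clustering) and 23% (independence) of totals would have a blank. The change is worth making because the rule is demonstrably mis-scaled for the primary outcome and the correction is nearly free, not because a large loss has been shown.

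**What to change.** Delete the dataset-wide 10% trigger. Make the plan's own cap the operative rule for outcome scales at follow-up: where no more than 30% of a participant's items on an instrument are blank (up to 3 of 13 RHS items), impute the items with mice or prorate the total, whatever the overall missing rate. Name which of the two is primary. Keep the comparison with and without imputation, and say that it is always run.

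For baseline RHS, state that the running variable is the score actually used for allocation and that it is not re-scored afterwards. Nothing is proposed here about scoring at screening.

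The cost is one or two sentences in the missing-data section and a few lines of code, with no new data. The downside is small: some totals will carry imputation error. If blanks cluster strongly, the gain is smaller too, because roughly half of the incomplete forms would exceed the cap (at p = 2% and ρ = 0.6, 2.4% of totals fall within it out of 5.1% with any blank).

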### Plans to give access to the full protocol, participant level-data and statistical code

The study protocol will be published in a peer reviewed journal. Participant-level outcome data and statistical codes may be shared in a public repository for replication under the condition that the anonymity of the participant can be guaranteed.

### Composition of the data monitoring committee, its role and reporting structure

Due to the minimal risk of implemented interventions no data monitoring committee is established.

### Adverse event reporting and harms

The likelihood of severe adverse events (SAE) due to referral or narrative exposure is expected to be low, indeed this is the gold standard in international guidelines (e.g. NICE, APA and AWMF). In this study, SAEs are defined as adverse events that result in death, life-threatening injury or damage of self or others, persistent or significant disability or dysfunctionality, or congenital anomaly and/or require further interventions to prevent permanent impairment or damage. SAEs during NAT will be reported to clinical supervisors and case management discussed with the principal investigators. Any SAE attributable to NAT will be reported in the final publication.

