**Severe stress (RHS ≥ 37 or acute danger to self or others)**
Individuals in this category likely meet the diagnostic criteria for a mental health disorder or present an immediate danger to themselves or others. In such cases, individuals are referred to a licensed psychotherapist for clinical assessment and guideline-based treatment. Referrals are made to various service providers, including psychosocial centres, collaborating private practitioners, licenced psycho-therapists, outpatient clinics and hospitals. In cases of immediate danger to self or others, referrals for inpatient treatment may be necessary and directed to specialised clinical services in the region (psychiatric hospitals, acute care units, or, when appropriate, law enforcement).

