### Criteria for discontinuing or modifying allocated interventions

In the event of danger to self or others, deterioration of trauma reactions or signs of other (comorbid) psychological symptoms, the client will be re-assigned to the red group and receive psychotherapeutic service or treatment at an acute care facility within the German health system. Thereafter, treatment delivery will follow the principles of the red group in full extent.

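### SAE reporting is tied to the NAT period and to attribution, so serious adverse events cannot be compared between NAT and its comparators

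*Protocol article*

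**What the plan says.** Four rules in the Protocol article bear on this point.

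- **Reporting route** (Adverse event reporting and harms): "SAEs during NAT will be reported to clinical supervisors and case management discussed with the principal investigators". No other route is given.
- **Publication** (same section): "Any SAE attributable to NAT will be reported in the final publication". No other commitment to publish SAEs is given, and no role is named to decide attribution.
- **Definition** (same section): "SAEs are defined as adverse events that result in death, life-threatening injury or damage of self or others, persistent or significant disability or dysfunctionality". Congenital anomaly is added, and then events that "require further interventions to prevent permanent impairment or damage". Inpatient admission is not named.
- **Oversight** (Composition of the data monitoring committee): "no data monitoring committee is established", on the ground of minimal risk. Under Who will be blinded, neither participants nor assessors are blinded.

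Two clinical sections describe events that the SAE rules need to classify. Table 2, severe stress, says: "In cases of immediate danger to self or others, referrals for inpatient treatment may be necessary". Criteria for discontinuing or modifying allocated interventions says that on danger or deterioration "the client will be re-assigned to the red group and receive psychotherapeutic service or treatment at an acute care facility", and that care from then on follows the red-group principles.

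**The concern.** A harms report is informative when events are counted in the same way in every group and over the same period, with causality recorded as an additional judgement. Here the stated window is the NAT period, and the stated filter for publication is a causal judgement by an unnamed, unblinded role.

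The lack of comparator counts cuts both ways. Background events in a distressed population could be read as harm from NAT. A true excess could be explained away as background. The protocol expects serious events to be rare and omits a monitoring committee for that reason, but these reporting rules would not supply the data to check that expectation for peer-delivered trauma work in this setting.

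**Working it through.** The protocol states no SAE rate, SAE sample size or SAE power, so there is no figure to reproduce. The check is a comparison of sections, followed by an illustration under assumptions.

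**1. Which groups and periods have a stated route.** Table 1 lists the comparators: awaiting NAT, waiting for or receiving psychotherapy, watchful waiting, and the same clients before NAT. None of these is a period during NAT. The time after NAT up to the follow-up at 6–9 months is not covered either. Comparator SAEs are therefore undescribed.

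**2. What happens on deterioration.** A client who worsens during NAT is re-assigned to the red group. An admission or self-harm event shortly afterwards is no longer plainly an event during NAT. The window can therefore close for the clients who have just deteriorated.

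**3. What reaches publication.** SAEs attributed to NAT are a subset of SAEs in NAT clients, so the published count can equal the full count or fall below it, never above it. The size of the shortfall cannot be derived from the document. The section on the coordinating centre shows that project leadership and counsellor supervision are partly the same people, and events go to supervisors and principal investigators.

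**4. Whether admission is an SAE.** An admission that averts permanent damage meets the last clause of the definition. An admission for assessment or short stabilisation may not. Whether an acute-care transfer under the discontinuation section counts depends on the reader.

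**5. What is compared between groups.**
- Hypothesis 2a compares how many clients need specialised treatment at 6–9 months, with chi-squared tests of more or less intensive treatment.
- The RHS-15 contrast in the regression discontinuity analysis is two-sided.
- The reliable change index can classify deterioration.
- Table 1 counts improving and deteriorating clients against watchful waiting.

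These measures show worsening. None of them counts deaths, self-harm or admissions as such, and the RHS-15 measures need a completed assessment.

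**6. What complete SAE data could show.** Expected participation is 30–50% of about 1,500: 0.30 × 1,500 = 450 and 0.50 × 1,500 = 750, over all severity groups. The rates and group sizes below are assumptions. The upper size, 750 / 2 = 375 per group, is generous because it splits the largest expected sample into only two groups.

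Power (two-sided 5%) = Φ{[d√n − 1.96√(2p̄(1 − p̄))] / √(p₁(1 − p₁) + p₂(1 − p₂))}, with d = p₂ − p₁ and p̄ the mean of the two rates.

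| Assumed SAE rates | Power, n = 100 per group | Power, n = 375 per group | n per group for 80% |
|---|---|---|---|
| 1% vs 3% | 17% | 50% | 769 |
| 2% vs 6% | 30% | 80% | 376 |

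Worked cell (1% vs 3%, n = 100): d√n = 0.02 × 10 = 0.200; 1.96 × √0.0392 = 0.388; √0.0390 = 0.197; (0.200 − 0.388) / 0.197 ≈ −0.95; Φ ≈ 0.17.

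With no events in a group, the one-sided 95% upper bound is 1 − 0.05^(1/n): 2.95% at n = 100 and 0.80% at n = 375.

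In most of these cases a by-group table gives counts and intervals, not an adequately powered test.

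**The case against.** The strongest reply is that the rules are being read too narrowly.

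- **The publication sentence sets a minimum.** It does not forbid reporting other SAEs. This stands. The criticism is that full compliance still permits a report confined to attributed events.
- **The reporting sentence describes an escalation route, and a condensed article may leave collection in other groups to a fuller document.** This also stands. A reader might infer that nothing is collected in the comparators, or that their SAE count is zero by construction. The document says neither. The publication rule and the definition are fixed in this text, however, and can be judged as written.
- **NAT could mean the whole programme.** Eligibility criteria call the screening NAT step 1, so the window might cover everyone. But the abbreviation list defines NAT as Narrative Trauma Work, and Table 1 uses it for the treatment condition. Even on the wide reading, the attribution filter remains.
- **The clause on further interventions covers admissions.** It covers some of them, so a reader who infers that admission lies wholly outside the definition goes too far. The boundary is unclear.
- **Harm is compared elsewhere.** This is correct. A reader might infer that the trial cannot show harm from NAT relative to its comparators. The planned comparisons of symptoms and escalation of care contradict that.
- **A by-group SAE comparison would be confounded and weak.** The red and green groups differ from NAT clients in baseline severity by design, and power is low. This limits what the table can claim, but it does not justify leaving events out of it.

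The lack of a data monitoring committee has a stated reason and is not a fault in itself. It matters here because no independent role reviews attribution.

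**Conclusion.** The concern holds in this form: followed as written, the plan permits a one-sided, attribution-filtered SAE record and does not allow serious adverse events to be compared between NAT and its comparators. Re-assignment of clients who deteriorate makes the gap worse. The definition and the clinical sections leave it open whether an inpatient or acute-care admission is an SAE.

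The number of SAEs that would go unpublished cannot be derived. The power figures rest on assumed rates and group sizes, and they show only that complete data would serve description more than testing. The conclusion also assumes that no fuller safety procedure overrides the published rules. The point is worth correcting before reporting, but it does not threaten the primary analysis.

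**What to change.** - **Collection.** Record SAEs in the same way in all groups from baseline to the last follow-up, including after re-assignment and after the end of NAT. All participants are already invited to the 6–9 month interview, so one question there is the base. Clients who died or are in hospital will not attend, so the planned documentation of reasons for missing data should capture SAEs as a reason.
- **Definition.** State whether inpatient or acute-care admission counts as an SAE, so that the adverse event section, Table 2 and the discontinuation criteria agree.
- **Attribution.** Name the role that judges it, and record the judgement for each event.
- **Publication.** Report all SAEs by group, regardless of attribution, with attribution as an added column. Present the table as descriptive, with intervals, because the groups differ in baseline severity and power is low.

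The cost is a few protocol sentences, slightly more recording work, one extra question at an existing contact and one extra table.
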